### 2.8.1 Modified Ashworth Scale (MAS) [53]

The MAS was used to evaluate muscle spasticity in the lower limbs. MAS evaluation involves the rater manually moving a limb through the range of motion to passively stretch specific muscle groups and a six-point ordinal scale for grading the resistance encountered during such passive muscle stretching. MAS grades of spasticity are as follows: 0 = normal muscle tone; 1 = slight increase in muscle tone, manifested by catch and release or by minimal resistance at the end; 1+ = slight increase in muscle tone, manifested by a catch, followed by minimal resistance throughout; 2 = more marked increase in muscle tone, but limb easily flexed; 3 = considerable increase in muscle tone, passive movement difficult; and 4 = limb rigid in flexion or extension.

#### Modified Ashworth Scale

| Grade | Description                                                                                                                                                                             |
|-------|-----------------------------------------------------------------------------------------------------------------------------------------------------------------------------------------|
| 0     | No increase in muscle tone                                                                                                                                              |
| 1     | Slight increase in muscle tone, manifested by a catch and release or by minimal resistance at the end of the range of motion when the affected part(s) is moved in flexion or extension |
| 1+    | Slight increase in muscle tone, manifested by a catch, followed by minimal resistance throughout the remainder (less than half) of the Range of Movement                                |
| 2     | More marked increase in muscle tone through most of the Range of Movement, but affected part(s) easily moved                                                                            |
| 3     | Considerable increase in muscle tone, passive movement difficult                                                                                                                        |

|   |                                                |
|---|------------------------------------------------|
| 4 | Affected part(s) rigid in flexion or extension |
|---|------------------------------------------------|

### 2.8.2 Modified Tardieu Scale (MTS) [55,56]

MTS will be used to evaluate the degree of spasticity in the lower limbs of participants. The MTS uses standardized procedures to measure quality of muscle reaction at specified velocities (i.e., fast stretch and slow controlled motion). During the fast stretch, the particular angle at which “catch” [57] occurs from hyperactive stretch reflex is called R1, also known as angle of muscle reaction. During the slow controlled motion, the passive range of motion (PROM) is assessed (called R2), representing the muscle length at rest and recorded as an angle. The difference between the two measures (i.e.,  $R2 - R1$ ; dynamic component of spasticity) is recorded as R. A large difference between R1 and R2 suggests a large dynamic component with a greater capacity for change or improvement. A small difference between R1 and R2 suggests a predominantly fixed contracture in the muscle with a poorer capacity for change.

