#### Modified Tardieu Scale

| Grade | Description                                                                                              |
|-------|----------------------------------------------------------------------------------------------------------|
| 0     | No resistance throughout the course of the passive movement.                                             |
| 1     | Slight resistance throughout the course of the passive movement, with no clear catch at a precise angle. |
| 2     | Clear catch at a precise angle, interrupting the passive movement, followed by a release.                |
| 3     | Fatigable clonus (<10 seconds when maintaining pressure) occurring at a precise angle.                   |
| 4     | Infatigable clonus (>>10 seconds when maintaining pressure) occurring at a precise angle.                |
| 5     | Joint is immovable                                                                                       |

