## **Section 5: Statistical analysis**

SPSS v. 20.0 will be used for statistical analysis of the data. The data will be entered into Excel tables by double entry and checking to establish the database. The data of MAS and

MTS scales will be described in terms of means  $\pm$  standard deviation. If the data of MAS , and MTS scale did not conform to the conditions of normal distribution and homogeneity of variance, the Mann-Whitney test will be used; if the data of MAS and MTS scale did conformed to the conditions of normal distribution and homogeneity of variance, then independent sample t-test will be used. Pearson correlation analysis will be used for the correlation analysis between the GMFCS grade, gender and age and muscle tone after treatment in the Experiment Group. Either one-way ANOVA or Chi-squared test will be used for inter-group data comparison. A p-value less than 0.05 will be considered statistically significant.

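### The only score derived from the Tardieu angles, R = R2 - R1, is ambiguous if compared on its own, and the protocol names neither the MTS quantity compared nor its direction of benefit

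*Protocol*

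**What the plan says.** Protocol section 2.8.2 gives the purpose of the scale: "MTS will be used to evaluate the degree of spasticity in the lower limbs of participants". It defines two angles. The fast stretch gives the catch, which "occurs from hyperactive stretch reflex is called R1, also known as angle of muscle reaction". The slow movement gives the passive range R2, described as "representing the muscle length at rest and recorded as an angle". The difference R2 - R1 is then given a name of its own: "dynamic component of spasticity) is recorded as R".

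The section interprets both ends of R. For a high value: "A large difference between R1 and R2 suggests a large dynamic component with a greater capacity for change or improvement". For a low value: "A small difference between R1 and R2 suggests a predominantly fixed contracture in the muscle with a poorer capacity for change".

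The table that follows adds a 0 to 5 grade for the quality of the muscle reaction; grade 2, for example, is "Clear catch at a precise angle, interrupting the passive movement, followed by a release".

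Section 5 (Statistical analysis) says that the MAS and "MTS scales will be described in terms of means" and standard deviations. The arms are compared by an independent-sample t-test, or by Mann-Whitney if normality or equal variance fails. It does not say whether the MTS quantity compared is R1, R2, R or the grade, does not state a direction of benefit, and mentions no baseline adjustment. Section 2.6 names the Modified Ashworth Scale (MAS) as the primary outcome measure.

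**The concern.** A trial that sets out to improve spasticity needs an outcome on which improvement has one direction. As the dynamic component, a lower R should be good. But the only meaning that section 2.8.2 attaches to a low R is fixed contracture with little room to change, which is a poor state. The same fall in R can therefore come from a later catch (R1 up) or from lost range (R2 down).

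Contracture is not remote from this population: Section 1 describes it as a frequent consequence of spasticity and lists slowing of musculoskeletal deformity among the aims of treating it.

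If R is compared alone, a significant difference would not show which angle moved, and a null result could coexist with gains in both. With the component unnamed, R1, R2, R and the grade also all remain available once the data are seen.

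**Working it through.** The protocol states no figure on this point, so there is none to reproduce. The check has three parts.

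**1. Arithmetic of the score.** From section 2.8.2, R = R2 - R1, so change in R = change in R2 - change in R1. The starting angles below are illustrative and are not in the protocol.

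| Case | R1 | R2 | R | Change in R |
|---|---|---|---|---|
| Start | 10 | 30 | 20 | – |
| R1 rises by 10 (later catch) | 20 | 30 | 10 | -10 |
| R2 falls by 10 (lost range) | 10 | 20 | 10 | -10 |
| Both rise by 10 | 20 | 40 | 20 | 0 |
| Both fall by 10 | 0 | 20 | 20 | 0 |
| R1 rises by 5, R2 by 10 | 15 | 40 | 25 | +5 |

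The second and third rows have the same R. The fourth and fifth rows have opposite courses and the same R. In the last row both angles gain, yet R rises.

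**2. What a between-arm test would show.** Simulation with 30 per arm, two-sided t-test at 0.05 and 10,000 repeats. Assumed, not from the protocol: SD of change 8 degrees, correlation 0.5 between the changes in R1 and R2, and arm differences of 7 degrees.

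| True arm difference | R significant | R1 significant |
|---|---|---|
| R1 +7 only | 92% (lower) | 92% (higher) |
| R2 -7 only | 92% (lower) | about 5% (chance) |
| R1 +7 and R2 +7 | about 5% (chance) | 91% (higher) |
| R1 -7 and R2 -7 | about 5% (chance) | 91% (lower) |

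The second row assumes that R1 stays put when range is lost.

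**3. Power on R against power on R1.** Section 2.6 gives 30 per arm, power 0.90 and alpha 0.05, but for the MAS and without an effect size. By the exact t-test, the standardised difference that 30 per arm detects with power 0.90 is d = 0.851. I take this as an assumed R1 effect, so power on R1 is 0.90 by construction.

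Let rho be the R1-R2 correlation, with equal SDs, and let s be the share of the R1 gain that R2 also shows. Then

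- SD(R) = SD × sqrt(2(1 - rho))
- effect on R = 0.851 × (1 - s) / sqrt(2(1 - rho))

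Worked case, rho = 0.5 and s = 0.50: sqrt(2 × 0.5) = 1, so the effect is 0.851 × 0.50 = 0.426 and the power is 0.37.

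| rho | s = 25% | s = 50% | s = 75% |
|---|---|---|---|
| 0.3 | 0.54 | 0.28 | 0.11 |
| 0.5 | 0.68 | 0.37 | 0.13 |
| 0.7 | 0.88 | 0.55 | 0.18 |
| 0.8 | 0.97 | 0.73 | 0.25 |
| 0.9 | 1.00 | 0.95 | 0.44 |

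Power on R falls as R2 moves with R1, but it rises with the correlation, because differencing removes shared variation. R has less power than R1 in most cells and more in three (rho = 0.8 with s = 25%; rho = 0.9 with s = 25% or 50%).

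**The case against.** The strongest reply is that the protocol never says R is the quantity tested. Both angles are recorded in their own right, a grade is listed too, Section 5 speaks only of the MTS scale, and the choice of component may be made in an analysis plan that is not shown. That stands, and it makes the point conditional. It does not remove it: the protocol itself derives R as its one score from the angles and gives a low value an adverse meaning.

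Second, the two interpretive sentences concern capacity for change at a single assessment. They do not say how to read a change after treatment, and the label of dynamic component suggests that lower is intended to be better. This is a fair reading, but the direction is still left to inference.

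Third, a reader might infer that the trial will count contracture as benefit. The documents do not support that. Randomisation balances background loss of range, and both arms receive the same passive stretching and massage (section 3.2). False benefit would need stimulation to cost R2 more than R1, and nothing in the protocol gives reason to expect it within 12 weeks.

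Fourth, a reader might infer that R is bound to lose power and that R1 should replace it as the only tested angle. The correlation table refutes the first part. On the second, R1 is itself affected by muscle length, so it is not a clean measure of spasticity either. If both angles rise equally, one can argue that range improved while the dynamic component did not. For that reason both angles are needed.

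**Conclusion.** The point holds in conditional form. If R is the MTS quantity compared, R alone cannot separate a later catch from lost range, and it misses equal gains in both angles. That follows from the definition in section 2.8.2 and needs no assumption. Whether R will be compared alone is not stated.

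The practical size is unknown. The protocol gives no contracture rate, no SD for either angle and no R1-R2 correlation. Under the assumptions shown, power on R lies between about 0.11 and 1.00, against 0.90 on R1, so no single figure for power loss can be defended.

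The effect is confined to a supportive measure; the MAS comparison is untouched. It would go too far to say that the MTS cannot address the objective: it cannot do so on R alone, and the angles that would resolve the ambiguity are already recorded. The change is worth making because it costs so little.

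**What to change.** In section 2.8.2 and Section 5:

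- Compare R1 and R2 between arms as separate quantities, each adjusted for its own baseline value and reported with an estimate and confidence interval, in place of an unadjusted test on an unnamed MTS score.
- State the angle convention, and that under it higher R1 and higher R2 are benefit.
- State that any difference in R is interpreted only together with the R1 and R2 results.

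The cost is wording. Both angles are part of the MTS assessment planned at baseline and after treatment (sections 2.8 and 2.8.2), so no new measurement or visit is needed. The downside is a few more reported estimates on a non-primary measure.

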#### Modified Tardieu Scale

| Grade | Description                                                                                              |
|-------|----------------------------------------------------------------------------------------------------------|
| 0     | No resistance throughout the course of the passive movement.                                             |
| 1     | Slight resistance throughout the course of the passive movement, with no clear catch at a precise angle. |
| 2     | Clear catch at a precise angle, interrupting the passive movement, followed by a release.                |
| 3     | Fatigable clonus (<10 seconds when maintaining pressure) occurring at a precise angle.                   |
| 4     | Infatigable clonus (>>10 seconds when maintaining pressure) occurring at a precise angle.                |
| 5     | Joint is immovable                                                                                       |

## Section 3: Intervention

### 3.1 Combined tPCS and TENS therapy

Two therapists with more than 5 years’ experience in electrical stimulation will be in charge of the treatment of subjects with the combined tPCS and TENS therapy in the Experiment group. The multichannel pulsed current stimulator (YQ-D507; Yiqi

Biotechnology Co. Ltd, China) will be used and the stimulation procedure will be carried out using six pairs of (6\*9 cm) surface gel electrodes. tPCS: The first pair of electrodes will be used for cerebello-cerebral stimulation, with the anode electrode positioned over Cz (according to the 10–20 International Electroencephalogram System [60]), covering the Baihui acupoint, and cathode electrode positioned horizontally to cover the cerebellum region, coinciding with Oz (according to the 10–20 International Electroencephalogram System [58]; the bottom edge centered over the inion (Figure 2, 1+ and 1–). The skin of the scalp was required to be cleaned with saline prior to electrode placement. Stimulating current intensity was set to 1 mA. TENS: The second to sixth pairs of electrodes were used for afferent stimulation of the spinal cord and targeted muscle in the lower limbs. The second pair of electrodes was placed on the cervicothoracic region of the spine, with the anode covering C6–C7 and cathode covering T1–T2 [59] (Figure 2, 2+ and 2–). The third pair of electrodes was placed on the thoracolumbar region, with the anode covering T11–12 and cathode covering L4–L5 [31, 32] (Figure 2, 3+ and 3–). The fourth pair of electrodes were placed on the adductor longus muscles of the lower limbs (Figure 2, 4+ and 4–). The fifth pair of electrode pads (Figure 2, 5+ and 5–) were placed on the rectus femoris muscles of the lower limbs. The sixth pair of electrode pads (Figure 2, 6+ and 6–) were placed on the gastrocnemius muscles of the lower limbs. The specific strength of the second to sixth pairs of electrodes was adjusted according to the degree of tolerance of individual children, with current intensity varying from 0 to 10 mA. Time of stimulation for all six pairs is 30 minutes each session, the device has one button controlling each pair of electrodes that allows the operator to control the intensity of the current. Stimulation will be raised from 0 to the desired level and diminished to 0 in the final one second. Combined tPCS and TENS therapy will be done 5 times a week, for 12 consecutive weeks, totaling 60 sessions.

[figure not shown]

**Fig 2: Position of electrodes patches during mTPCS stimulation**

The output parameters of mTPCS in this study were as follows:

- tPCS (1st electrode pair) intensity: 1 mA
- TENS (2nd –6th electrode pairs) intensity: 0–10 mA
- Pulse Width of current: 140ms
- High Frequency: 400 Hz
- Waveform: Unidirectional monophasic pulse square wave

### 3.2 Physical therapy

Physical therapy will be done by two physical therapists with more than five years' experience and will consist of passive stretching exercises and Chinese “Tui Na” massages [14] often used for children with SCP to reduce muscle stiffness, with a focus on lower limb muscles, it will not include other forms of electrical stimulation. Each physical therapy session will be 30 minutes, carried out five times a week over twelve consecutive weeks. Physical therapy for the Experiment Group will be administered immediately after combined tPCS and TENS therapy, while the Control group will be given only physical therapy.

## Section 4: Safety Considerations

Safety issues will be identified a priori by the authors who, on average, have over 20 years of pediatric clinical experience in China. The tPCS used for cortical stimulation in the

study belonged to the category of low-intensity transcranial electrical stimulation (tES) and no serious adverse events (SAEs) have been reported so far in over 18,000 sessions of low-intensity tES administered to healthy subjects, as well as in neurological and psychiatric patients [60]. Moderate adverse events (AEs) in tES, as defined by the necessity to intervene, are rare, and include skin burns due to suboptimal electrode-skin contact. Mild side effects in tES include itching, tingling, burning sensations, and transient redness may occur during treatment [61-65]. In a systematic review by Bikson et al [66], it was reported that at least 2800 sessions of tDCS have been applied across nearly 500 child subjects covering medical conditions such as cerebral palsy, stroke, encephalitis, epilepsy, schizophrenia and attention deficit hyperactivity [67-74], and no serious adverse effects have been reported. Furthermore, a study by Jaberzadeh that compared tPCS to tDCS showed that participants tolerated a-tPCS better than the conventional a-tDCS [15].

For safety of tES on children, the recommended dose needs to compensate for thinner skull and lower resistance [75, 76]. Mattai et al. [77] explored the safety and tolerability of tDCS in children with childhood-onset schizophrenia and found that 10 sessions of 2 mA tDCS for 20 min, 25 cm electrodes, was administered without incident in the test subjects with no serious side effects. In the present study, tPCS (Unidirectional monophasic pulse square wave) will be controlled at 1mA, 30mins per session, which is within the confines of conventional tES and safe for children. In addition, our study design passed the safety review conducted by Guangzhou City Social Welfare Institute Rehabilitation Hospital Ethics committee, who gave approval for this study.

As a safety monitoring plan, two experienced pediatric nurses will be assigned to systematically observe all participants during the study for adverse reactions such as seizure, nausea, behavioral changes, or severe discomfort, and at the end of each treatment session, the children and/ or their caregivers in the Experiment group will be asked about side effects. In the event any Adverse Event occurs, there will be immediate termination of treatment and AE will be recorded and reported accordingly.

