## **Section 2: Methods/Design**

### **2.1 Objective of the Study**

The objective of the proposed study is to test the effectiveness of a combination of transcranial pulsed current stimulation (tPCS) and transcutaneous electrical nerve stimulation (TENS) as an innovative strategy for improving lower limb spasticity in children with spastic cerebral palsy (SCP) categorized on levels III–V of the Gross Motor Function Classification System (GMFCS), who face increased challenges in spasticity management and currently lacking treatment options with low/no side effects.

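### Side effects are asked about after each session in the Experiment group only, so mild complaints are not collected comparably in the two arms

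*Protocol*

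**What the plan says.** Section 4 of the Protocol (Safety Considerations) sets up two ways of finding adverse events.

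- **Observation, both arms.** Two paediatric nurses are to "systematically observe all participants during the study for adverse reactions such as seizure, nausea, behavioral changes, or severe discomfort".
- **Questioning, one arm.** At the end of each treatment session the children and/or "their caregivers in the Experiment group will be asked about side effects". Nothing equivalent is specified for the Control group.

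The same section says of a recorded event: "In the event any Adverse Event occurs, there will be immediate termination of treatment and AE will be recorded and reported accordingly". On what to expect from stimulation it says: "Mild side effects in tES include itching, tingling, burning sensations, and transient redness may occur during treatment".

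The two arms have the same contact schedule. For stimulation, section 3.1 says: "Combined tPCS and TENS therapy will be done 5 times a week, for 12 consecutive weeks, totaling 60 sessions". For physiotherapy, which both arms receive, section 3.2 says: "Each physical therapy session will be 30 minutes, carried out five times a week over twelve consecutive weeks".

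**The concern.** Asking finds mild, subjective complaints that an observer often misses. If one arm is asked and the other only watched, the recorded rates differ even when the true rates are equal. The complaints at issue are those that can arise with or without electrodes, such as discomfort short of severe, nausea or a change in behaviour.

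Two things are at stake. First, a table of side effects by arm would tend to show an excess in the Experiment arm that comes partly from how the events were collected. Second, children in the Experiment group receive physiotherapy immediately after stimulation. Without a control group questioned in the same way, complaints due to physiotherapy or to the underlying condition cannot be separated from those due to stimulation.

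The safety data matter here because section 1.2 states that tPCS has not been studied in children with spastic cerebral palsy. Nothing else in the design offsets the asymmetry. There is no sham (section 2.7), and section 2.8 states blinding only for the MAS and MTS evaluators. Nor can a later analysis recover answers that were never requested.

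**Working it through.** The Protocol gives no adverse-event rate and no figure for capture, so there is no stated number to reproduce. The asymmetry can be counted from the text. The size of the bias can only be illustrated.

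**Count of enquiries.** 5 sessions per week × 12 weeks = 60 per child. Section 2.6 plans 70 participants, or 35 per arm at 1:1. If all sessions are completed, there are 60 × 35 = 2,100 planned enquiries in the Experiment arm and none specified in the Control arm.

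**Illustration: inputs (all assumptions except n).**
- p: true share of children with a mild event, the same in both arms; 10%, 30% or 50%.
- s_E: share of these captured with asking (Experiment arm); 90%.
- s_C: share captured by observation alone (Control arm); 70%, 50% or 30%. A value of 90% represents equal questioning.
- n = 35 per arm.

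**Formulas.** The recorded rates are p·s_E and p·s_C, so the recorded risk ratio is s_E / s_C whatever the value of p:
- 0.9 / 0.7 = 1.29
- 0.9 / 0.5 = 1.80
- 0.9 / 0.3 = 3.00

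The chance of a false difference is the exact probability that a two-sided Fisher test gives P < 0.05. It is summed over all pairs of counts from Binomial(35, p·s_E) and Binomial(35, p·s_C).

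| Control capture s_C | Recorded risk ratio | p = 10% | p = 30% | p = 50% |
|---|---|---|---|---|
| 90% (equal) | 1.00 | 1.1% | 2.7% | 2.5% |
| 70% | 1.29 | 1.2% | 5.2% | 9.0% |
| 50% | 1.80 | 2.0% | 15.6% | 33.8% |
| 30% | 3.00 | 3.6% | 39.5% | 72.7% |

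With p = 30% and s_C = 30%, for example, the recorded rates are 0.30 × 0.9 = 27% and 0.30 × 0.3 = 9%.

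With 30 per arm (the evaluable target in section 2.6) the pattern is the same. For s_C of 70%, 50% and 30% the figures are 4.6%, 12.7% and 31.3% at p = 30%, and 7.6%, 27.2% and 64.5% at p = 50%.

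Capture in the Control arm drives the result, and the document gives no basis for choosing a value.

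**The case against.** The strongest reply is that no adverse-event comparison is planned. The objective and hypothesis (sections 2.1 and 2.2) concern spasticity. Section 5 names MAS and MTS, and its general sentence on comparing groups does not mention adverse events. This stands. A reader might infer that a prespecified test is biased, but the document contains none; the problem lies in any descriptive or later comparison.

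Four further points limit the concern.

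- **Overt events.** A reader might infer that the trial has no usable control rate at all, or that background seizures would be credited to stimulation. The text does not support this, because nurses observe both arms for seizure, nausea, behavioural change and severe discomfort. The gap is in milder complaints.
- **Electrode sensations.** Itching or tingling under an electrode cannot occur in children without electrodes, so asking about those in one arm does little harm.
- **Direction.** Extra questioning raises the recorded events of the experimental treatment. It does not hide harm or flatter tolerability. The cost is over-attribution to stimulation.
- **Rationale.** The phrase "currently lacking treatment options with low/no side effects" in section 2.1 describes existing options. It is not a claim of better tolerability than physiotherapy.

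It is also tempting to say that unequal questioning will cause unequal stopping, because the Protocol ties termination to any adverse event. That is only a possibility. Section 4 does not say whether the session or the whole course of treatment ends, and section 2.5.3 mentions serious adverse reactions as a ground for drop-out. These passages need to be reconciled before the consequence can be judged.

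What survives is that the restriction to one arm is explicit and concerns how data are collected, which a statistical analysis plan cannot repair afterwards.

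**Conclusion.** The concern holds in a limited form. Mild complaints that do not arise under an electrode are sought actively in one arm and only by observation in the other, so their recorded rates will not be comparable. A between-arm description would tend to overstate the excess in the Experiment arm.

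The possible size runs from negligible to large. Under the assumptions above, the recorded risk ratio is 1.3–3.0 where the truth is 1.0. A Fisher test at 35 per arm would be falsely significant in about 5–73% of trials for true rates of 30–50%, and in fewer than 4% at a true rate of 10%. The upper end needs both a common event and poor capture by observation, and should not be quoted alone. The event rates, the capture rates and the choice of test are mine, not the Protocol's.

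The point is worth correcting because the remedy is cheap, but it does not threaten the primary comparison as the document stands.

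**What to change.** Amend the safety monitoring paragraph in Section 4 so that children and/or caregivers in both groups are asked the same side-effect questions, on the same form, at the end of every session. Questions specific to electrode sites can stay in the Experiment group if they are recorded as a separate item. Report solicited and observed events separately by arm; the table layout can be left to the statistical analysis plan.

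In the same amendment, reconcile the scope of the termination sentence in Section 4 with the drop-out criteria in section 2.5.3, so that it is clear what a recorded event leads to in each arm.

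With equal questioning at the assumed 90% capture, the expected recorded risk ratio returns to 1.0 and the false-positive probability to between 0.8% and 2.7% (30 or 35 per arm, true rates of 10–50%).

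The cost is a short extra enquiry at each control session, up to 60 per child, which the nurses already assigned to observe both groups could make. No treatment, visit or endpoint changes.

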### **2.5.3 Drop-out criteria**

Subjects who voluntarily terminated treatment during the course of treatment; subjects who did not receive treatment according to plan, either due to poor compliance or non-cooperation; and subjects who were not suitable to continue the trial due to serious adverse reactions or appearance of other accompanying diseases.

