## 2.8 Assessment

Evaluations using Modified Ashworth Scale (MAS) and Modified Tardieu Scale (MTS) will be conducted on all participants by two qualified rehabilitation doctors who have been involved in clinical work of pediatric rehabilitation for more than five years. The evaluators are blinded to the allocation of the children to the two groups and did not participate in the treatment of the subjects. A baseline evaluation and a post-treatment evaluation will be held. Both baseline and post-treatment evaluation will be conducted in a designated evaluation room that is spacious, quiet and bright, as follows:

- Baseline evaluation: three days prior to intervention
- Post-treatment evaluation: three days following last session of treatment
- Each scale will be repeatedly measured 3 times each time. Each score was the average of the three measurements.

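### The adverse-event stop has no stated scope and the MAS/MTS evaluation is timed from the last session, so a child stopped early could be evaluated weeks before the others, or not at all

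*Protocol*

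**What the plan says.** Protocol Section 4 (Safety Considerations) sets the rule: "In the event any Adverse Event occurs, there will be immediate termination of treatment and AE will be recorded and reported accordingly". It gives no severity threshold, no scope and no rule for restarting. The same section has two nurses "systematically observe all participants during the study for adverse reactions such as seizure, nausea, behavioral changes, or severe discomfort", and adds that "at the end of each treatment session, the children and/ or their caregivers in the Experiment group will be asked about side effects".

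Section 2.5.3 lists the drop-out grounds. One is "Subjects who voluntarily terminated treatment during the course of treatment". Another is "subjects who were not suitable to continue the trial due to serious adverse reactions or appearance of other accompanying diseases". The third, treatment not given as planned, is confined to poor compliance or lack of cooperation.

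Section 2.8 fixes the outcome time: "Post-treatment evaluation: three days following last session of treatment". There is one baseline and one post-treatment evaluation, and no separate date for a child who stops early.

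Section 3.1 plans 60 stimulation sessions, five a week for 12 weeks, for the Experiment Group. Section 3.2 covers physical therapy in both groups: "Each physical therapy session will be 30 minutes, carried out five times a week over twelve consecutive weeks". It also says "Physical therapy for the Experiment Group will be administered immediately after combined tPCS and TENS therapy", but not what happens to physical therapy once stimulation has been stopped.

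**The concern.** Three provisions meet badly. Section 4 stops treatment for any adverse event. Section 2.5.3 treats an adverse reaction as a drop-out ground only when it is serious. Section 2.8 ties the evaluation to the last session. Nausea and severe discomfort are on the Section 4 watch list and can be non-serious. A child stopped for one of these is not clearly a drop-out and not clearly still in the trial. If all treatment has ended, that child's evaluation falls due three days later.

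The two groups are not equally exposed to this. Control children receive physiotherapy only (Section 2.7), and the end-of-session questioning covers the Experiment Group only. If stopped children go unmeasured, the loss is concentrated in one group and related to how well treatment is tolerated. If they are evaluated early, time since baseline differs between the groups. Either could bias the comparison on the Modified Ashworth Scale (MAS) and Modified Tardieu Scale (MTS).

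**Working it through.** **1. What each scope would imply**

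| What ends | Evaluation under Section 2.8 |
|---|---|
| The session only | On time |
| Stimulation only; physical therapy runs to week 12 | On time, if the last session means the last physical therapy session |
| The whole course, including physical therapy | Three days after the early stop, or not done if the child is treated as having left |

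Only the third row causes the problem, and the protocol does not choose between the rows.

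**2. How early the evaluation would be (third row)**

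Inputs from Section 3.1: 60 sessions, 5 per week. Weeks early = (60 − stop session)/5.
- Stop at session 15: 45/5 = 9 weeks
- Stop at session 30: 30/5 = 6 weeks
- Stop at session 45: 15/5 = 3 weeks

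**3. The plan's sample size, as a yardstick**

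Section 2.6 gives 60 + 10 = 70 children. With 1:1 allocation that is 35 per group. The allowance of 10/70 = 14.3% covers both groups together.

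No standardized effect is stated. Solving a two-sided t-test at alpha 0.05 and power 0.90 gives d = 0.851 for 30 per group, and d = 0.977 for the 23 per group of the reference study. Both are used below because Section 2.6 does not settle which applies.

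**4. Possible bias (assumed inputs)**

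Let k of the 35 Experiment children stop and differ from the rest by delta SD. Leaving them out shifts the Experiment mean by (k/35) × delta. The same formula serves for early evaluation, with delta as the change missed before week 12. The protocol gives neither k nor delta. Take delta = 0.5 SD:
- k = 2: 2/35 × 0.5 = 0.029 SD, which is 3.4% of 0.851 or 2.9% of 0.977
- k = 5: 5/35 × 0.5 = 0.071 SD, which is 8.4% of 0.851 or 7.3% of 0.977

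The sign is not known. If the lost children would have done worse than average, dropping them flatters the Experiment Group. If early evaluation misses later improvement, it works against that group.

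For scale, if one event ends the course and events are independent across 60 sessions, the expected number stopped is 35 × [1 − (1 − p)^60]. An assumed p of 0.1% per session gives 2.0 children, and 0.25% gives 4.9.

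**5. Power (two-sided t-test, alpha 0.05, d = 0.851)**
- 35 vs 35: 0.939
- 2 Experiment children lost (33 vs 35): 0.933
- 5 Experiment children lost (30 vs 35): 0.921

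Loss of power is not the issue.

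**6. What keeping stopped children would cost**

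If benefit is proportional to sessions and k children stop halfway, the effect is multiplied by 1 − 0.5k/35.
- k = 2: 1 − 1/35 = 0.971, a 3% dilution
- k = 5: 1 − 2.5/35 = 0.929, a 7% dilution; power 0.903

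**The case against.** The strongest reply is that the stop may be meant narrowly. Elsewhere the protocol uses the word treatment for the delivery of current (Sections 1.2 and 4), and an instruction to act immediately fits switching the device off. Read so, an adverse event stops the stimulation, only a serious reaction ends participation, and Sections 4 and 2.5.3 agree. Section 3.2 schedules physical therapy for twelve weeks in both groups, so the last session could still fall in week 12. This stands as a possible reading. Section 4 also distinguishes a treatment session from treatment, and Section 2.5.3 speaks of terminating treatment for a drop-out, so the wider reading is open too. Neither is clearly better supported.

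A reader might infer more than the text carries:
- **That Section 2.5.3 makes every stopped child a drop-out.** It does not: among adverse reactions it names only serious ones. Nor does it say that drop-outs go unmeasured or are left out of the analysis, which an SAP may settle.
- **That the loss would be purely one-sided.** Nurses observe all participants, so a Control child could also be stopped.
- **That trivial tingling would trigger the stop.** Section 4 lists such sensations as mild side effects, apart from adverse events needing intervention.
- **That the bias could reach about 30% of the effect.** That needs 9 of 35 children stopped and a difference of 1.0 SD together (9/35 × 1.0 = 0.257 SD; 0.257/0.851 = 30%). Section 4 calls moderate adverse events of transcranial stimulation rare, and nothing in the protocol supports a 1.0 SD difference.

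What survives is that no section fixes a week-12 evaluation for a child who stops.

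**Conclusion.** The point holds as a cheap improvement, with medium confidence. The scope of the stop is undefined, a child stopped for a non-serious event has no clear status, and the stated evaluation rule follows the last session. Bias arises only if the stop ends the whole course, physical therapy included. It would then come mainly from the Experiment Group.

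Its size cannot be computed from the protocol. The illustration of 0.03 to 0.07 SD rests on assumed values: 2 to 5 of 35 children stopped, differing by 0.5 SD. The protocol does not support saying that bias will occur, that it is large, or that it has a known direction.

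**What to change.** Leave the safety stop as strict as it is, and leave any severity threshold to the investigators and the ethics committee. In Section 4, add a phrase saying what ends: the session, the stimulation or the course.

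In Sections 2.5.3 and 2.8, state that a child whose stimulation is stopped for an adverse event:
- continues physical therapy where this is safe;
- stays in follow-up in the allocated group;
- has the MAS and MTS evaluation at the planned end of the 12 weeks, three days after the scheduled last session, whenever the actual last session took place.

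How these data enter the analysis can be left to the SAP.

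The cost is a short amendment with ethics review and a scheduled evaluation for each of the few stopped children. The statistical price is the dilution from partly treated children shown above. With 5 half-treated children retained, power at d = 0.851 is 0.90, against 0.92 if those 5 were dropped. That is a modest price for removing a treatment-related difference in who is measured and when.
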